#### Data storage

The project manager, investigators and other project staff are responsible for maintaining a comprehensive and centralised bibliographic filing system of all study-related, essential documentation, suitable for inspection at any time by the approving HREC or applicable regulatory authorities.

A detailed data management plan will be completed and will ensure that all document data will be stored on hard disk drives. These computers will be networked to a file storage server, where an automated batch file copy procedure will back up the entire hard disk drive of each computer daily.

#### Data retention

Study records will be retained as per the Queensland Government University Sector Retention and Disposal Schedule. At the end of the study, final, non-identifiable data sets will be deposited in QUT’s Research Data Storage System. In line with publication embargoes and requirements, we will generate a document object identifier for each non-identifiable data set and make this record publicly accessible.

#### Data access

Processes for data access will be established in the data management plan. During the study, only members of the study team will access patient data.

#### Recruitment and consent

#### Recruitment

Potential participants will be identified based on the referral letter sent from their GP to the hepatology clinic. Potentially eligible participants will be sent a letter containing an invitation to participate and the contact details of a study nurse.

NEGATIVE OR NO RESPONSE: If no response to the initial letter is received after 2 weeks, a study nurse will contact the patient by phone. If the potential participant does not answer the phone, an SMS will be sent from a study phone to their mobile, informing them that it was a study nurse who called, and providing a brief explanation of the study and contact information. If at any stage of this process they state they are not interested, they will not be contacted again.

POSITIVE RESPONSE: Those interested in participating will be able to call a study nurse to discuss the trial. Interested participants will then be mailed the Participant Information and Consent Form, MBS/PBS consent forms, withdrawal form, study questionnaires, a $20 voucher and a reply-paid return envelope.

#### Consent

Potential participants who agree to be contacted after the recruitment process will be sent the study forms in the mail and asked to read, sign and return the forms using the reply-paid envelope. The study nurses will make one follow-up call, and SMS if not answered, to potential participants who have not returned the consent and enrolment questionnaires after 2 weeks. We will record the number of participants declining to consent and will also record the number of potential participants who could not be contacted.

#### Participant withdrawal

Participants will be able to withdraw with no negative consequences from further participation at any time, either in writing using the form provided to them at recruitment, or verbally to either a study team member and/or chief investigator. We will not collect any further data from the participant but will keep the data already collected unless the participant makes it clear that they do not wish this.

#### Randomisation

A 1:1 randomisation list will be created by the study statistician in the *R* software. The list will be stratified by health service (Sunshine Coast and Metro South) and will be in randomised blocks of size 6 and 8. This creates balanced groups over time and means that group sizes will be approximately equal if recruitment ends early. The list will be uploaded into the REDCap software [15]. Patients will be randomised once they have returned the signed consent form and questionnaires.

#### Blinding

It is challenging to hide the randomised group because this is an open-label study where both the participants and researchers will be aware of what group participants are in. Baseline data will be collected blind to randomised group, as it will be done prior to randomisation.

#### Safety evaluations

The following will be used to evaluate the safety of staff and patients involved in the study:
protocol deviation and adverse events reporting.incident and unanticipated problem monitoring.

#### Protocol deviations and adverse event reporting

The project manager is responsible for ensuring that all protocol deviations and adverse events are reported to the approving HREC and site Research Governance Officers. A protocol deviation is any noncompliance with the study protocol or HREC requirements and may be either on the part of the participant, the investigator, project team or the study site staff. Corrective actions will be implemented promptly.

#### Incident and unanticipated problem monitoring and reporting

The project manager is responsible for ensuring that all incidents and unanticipated problems observed by the investigator/s, project team or reported by sites are collected, reviewed and recorded in the source documents.

#### Monitoring

##### Data monitoring committee

We will recruit an independent study monitoring committee of three researchers - a clinician, a statistician, and one trialist - who have not collaborated with the chief investigator team in the past 5 years. This group will have controlled access to the study’s REDCap data collection site, where they will be able to view live reports on recruitment but not be able to see individual patient information. Recruitment reports show the current cumulative sample size and summary statistics on the sample’s baseline characteristics. We will prompt the data monitoring committee for 6-monthly feedback, share a one-page report on our progress against the milestones, and share this protocol with them.

### Statistical analysis

#### Sample size and statistical power

We have a minimum total sample size of 156 participants for our primary outcome of time to diagnosis, but we will aim for a sample size of 234. Two hundred and 34 participants will give us a 95% power to detect a 50% reduction in the primary outcome of time to diagnosis of high-risk disease. Our lower sample size of 156 gives us an 83% power. We used a two-sided 5% significance level. We assumed an average diagnosis time of 180 days in the usual care group, and a halving of this time in the intervention group. We assumed that 5% of participants would be censored due to death or loss to follow-up. The sample size was estimated by simulating survival data using the “sim.survdata” function from the “coxed” package in *R* using 1000 simulations [16]. We assumed a log-normal hazard function with a standard deviation of 10 days. The statistical code to run the sample size is available here: https://github.com/[name]/LOCATE. We assume that half of all patients approached will agree to participate, hence, we aim to approach 468 people.

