**Methods:**

We will conduct a 1:1 parallel randomised trial to compare two alternative models of care for NAFLD. Participants will be randomised to usual care or the LOCal Assessment and Triage Evaluation (LOCATE) model of care and followed for 1 year. We will recruit patients from the non-neighbouring Sunshine Coast and Metro South Hospital and Health Services (HHSs) in Queensland, Australia. Our primary outcome of interest is time to diagnosis of high-risk NAFLD, based on the number of participants in each arm of the study who receive a diagnosis of clinically significant fibrosis. Two hundred and 34 participants will give us a 95% power to detect a 50% reduction in the primary outcome of time to diagnosis of high-risk disease. We will also conduct an economic evaluation, evaluating the cost-effectiveness of the new model of care. We will also evaluate the implementation of the new model of care.

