## Background

Non-alcoholic fatty liver disease (NAFLD) is the most common type of chronic liver disease in Australia and its recent increase mirrors the obesity and type 2 diabetes epidemics [1, 2]. The prevalence of disease in Australia is approximately 30% of adults, comparable to other developed countries [3]. Currently, many patients who present to primary care with abnormal liver function tests or steatosis on liver ultrasound are referred for assessment in secondary care. Due to the large number of patients with NAFLD, this results in long waits for clinical and fibrosis assessment, placing unnecessary burden on the public hospital system. Depending on the presence of risk factors such as diabetes, 60 to 90% of patients with NAFLD do not have advanced fibrosis, are not at risk of chronic liver disease complications, and can be safely managed in primary care. At the other end of the risk scale, recent community-based studies have suggested that as many as 12 to 17% of primary care patients with NAFLD and type 2 diabetes may have clinically significant liver disease [4, 5]. The most important predictor of liver-related mortality is the extent of fibrosis – once NAFLD is identified, assessment of risk stratification is crucial to make decisions about management and referral. Due to the lack of risk stratification at primary care level, coupled with poor general practitioner knowledge about NAFLD [6], many patients with advanced disease may not undergo timely referral into secondary care. This exposes them to the risk of disease progression, decompensation and avoidable hospital admissions [7].

The predicted increases in NAFLD in the next decade will create demand on health services and have potentially large economic costs. As the number of NAFLD cases increase, the health system will incur increased costs associated with its diagnosis, management, and disease progression [8]. The estimated annual cost of liver diseases in Australia is $51 billion, of which NAFLD accounts for a considerable share [9], although few studies have reported economic outcomes [10].

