#### Patient exclusion criteria

Patients will be excluded if they:
Are pregnant.Have advanced cardiac disease or another terminal illness.Have high current alcohol consumption, defined as two or more standard drinks per day.Have Hepatitis B or C.Require priority review at the Hepatology Clinic, for instance, if liver imaging suggests cirrhosis or a focal liver lesion.Have been evaluated in a specialist hepatology clinic in the previous 12 months.Have plans to leave the area within the next 12 months.

The exclusion criteria are designed to reduce loss to follow-up and exclude patients who would be ineligible for a wider roll out of the service, or who require priority care and review.

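### The 95% and 83% power figures make no allowance for low-risk participants, who cannot have the primary event, so they are unsupported for the primary outcome

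*Protocol article*

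**What the plan says.** The section on sample size and statistical power states: "Two hundred and 34 participants will give us a 95% power to detect a 50% reduction in the primary outcome". For the minimum size it adds: "Our lower sample size of 156 gives us an 83% power". The abstract repeats the 95% claim. The inputs given are a two-sided 5% level, a mean of 180 days to diagnosis under usual care, half of that under LOCATE, a log-normal hazard with a standard deviation of 10 days, and 1000 simulations. On participants without an event it says only: "We assumed that 5% of participants would be censored due to death or loss to follow-up".

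Other sections fix who can have the event:

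- **Primary clinical outcome:** the event is a diagnosis of clinically significant fibrosis, meaning transient elastography over 8.0 kPa, timed from GP referral.
- **Low risk:** a reading under 8.0 kPa puts a participant in the low-risk class.
- **Per protocol definition:** the main analysis is by intention to treat.
- **Background:** it reports that "60 to 90% of patients with NAFLD do not have advanced fibrosis, are not at risk of chronic liver disease complications", and that "as many as 12 to 17% of primary care patients with NAFLD and type 2 diabetes may have clinically significant liver disease".

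**The concern.** Power in a time-to-event comparison is driven by the number of events. Someone whose liver stiffness is under 8.0 kPa contributes no event, however quickly the scan takes place. The purpose of the service is to sort a mainly low-risk referral population, yet the power statement makes no deduction for those participants.

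The figures in question are the only justification for the sample size, and 156 is put forward as an acceptable minimum. If the event count is far below what the power figures need, the trial could give an imprecise answer on its primary outcome while carrying a 95% power claim.

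**Working it through.** **Inputs.** From the sample-size section: N = 234 and 156, two-sided 5%, means of 180 and 90 days, 5% loss. From the randomisation and study-design sections: 1:1 allocation and 1 year of follow-up. Assumed here: a constant hazard, so that halving the mean gives a hazard ratio (HR) of 2, and a high-risk share *p*, which the protocol does not state.

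**Formula (Schoenfeld, 1:1).** Power = Φ(√D × ln 2 / 2 − 1.96), where D is the number of events and ln 2 / 2 = 0.3466.

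**Step 1: try to reproduce the stated figures, taking 5% as the only non-events.**

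- N = 234: D = 0.95 × 234 = 222.3. Φ(14.91 × 0.3466 − 1.96) = Φ(3.21) = 99.9%, against 95% stated.
- N = 156: D = 0.95 × 156 = 148.2. Φ(12.17 × 0.3466 − 1.96) = Φ(2.26) = 98.8%, against 83% stated.

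Neither figure is reproduced.

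**Step 2: events that the stated powers would need at HR 2.** D = (2 × (1.960 + z) / 0.6931)².

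- 95% (z = 1.645): (7.210 / 0.6931)² = 108.2, so 109 events. 109 / 234 = 47%.
- 83% (z = 0.954): (5.828 / 0.6931)² = 70.7, so 71 events. 71 / 156 = 46%.

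The two sizes agree on an event share of roughly 46%, which appears nowhere in the protocol. Alternatively, the stated powers fit 95% events with a weaker effect, HR about 1.6 (0.62 when inverted), which is not stated either.

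**Step 3: expected events and power over an assumed share.** D = N × 0.95 × *p*, at HR 2, with low-risk participants leaving the risk set at their assessment.

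| Share *p* | Events, N = 234 | Power | Events, N = 156 | Power |
|---|---|---|---|---|
| 10% | 22 | 37% | 15 | 27% |
| 17% | 38 | 57% | 25 | 41% |
| 25% | 56 | 73% | 37 | 56% |
| 40% | 89 | 90% | 59 | 76% |

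Example: 234 × 0.95 × 0.17 = 37.8. Φ(6.15 × 0.3466 − 1.96) = Φ(0.17) = 57%.

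**Step 4: sensitivity by simulation at N = 234** (means 180 and 90 days, 365-day follow-up, 5% loss, log-rank test, *p* from 10% to 40%).

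- Low-risk participants censored at assessment, exponential waits: about 36% to between 86% and 89%, close to the formula.
- The same handling with less variable waits (Weibull shape 1.5, assumed): about 63% to 99%.
- Low-risk participants kept at risk without an event to 12 months: about 6% to 19%, for either shape.

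The last result arises because both arms approach the same plateau. With exponential waits, the proportion of high-risk participants diagnosed by day 365 is 1 − exp(−365/180) = 87% under usual care and 1 − exp(−365/90) = 98% under LOCATE. At *p* = 40% and before loss, the arms therefore end at 0.40 × 87% = 35% and 0.40 × 98% = 39% of all randomised.

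**The case against.** The strongest reply is that the documents do not reveal what the simulation assumed. A reader might infer that it takes about 95% of participants to be diagnosed with high-risk disease. The protocol does not say so: the censoring sentence names two causes, death and loss, and gives no event proportion. Step 1 shows that 95% events do not return the stated powers at HR 2. A reader might also infer that the calculation really describes time to any fibrosis assessment. The code is cited but not shown, so that is conjecture. Both limits stand.

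The Background shares are also not the trial's share. The 60 to 90% figure concerns advanced fibrosis in NAFLD generally, whereas the event is clinically significant fibrosis. The 12 to 17% figure concerns primary care patients with type 2 diabetes, whereas participants here were referred because a GP was concerned. In the other direction, the exclusion criteria remove patients who "Require priority review at the Hepatology Clinic, for instance, if liver imaging suggests cirrhosis or a focal liver lesion", although the scan is still expected to find some cirrhosis. This stands too, and it is why the share is shown as a range.

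Finally, power can be adequate. With Weibull shape 1.5 and low-risk participants censored at assessment, it is 99% at a 40% share. The plan also reports estimates with 95% confidence intervals and aims to keep p-values out of external papers, which reduces the risk that a null result is misread.

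None of this supplies the missing allowance. At HR 2 the stated powers need about 46% of participants to have the event, above the top of the 10 to 40% that the Background suggests. The fit at a weaker effect needs more still.

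**Conclusion.** The point holds in this form: the 95% and 83% figures are attached to an outcome that low-risk participants cannot have, the section allows for no such participants, and the figures do not follow from the stated inputs under a constant hazard. The stated power is unsupported for the primary outcome. That it is wrong by a known amount cannot be shown.

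The size depends on three things that the protocol leaves open: the high-risk share, the shape of the waiting-time distribution, and how low-risk participants are treated after assessment. With censoring at assessment and HR 2, power at shares of 10 to 40% is about 37 to 90% at N = 234 and 27 to 76% at N = 156. Keeping low-risk participants at risk to 12 months takes it to about 6 to 19% at N = 234, so this choice matters as much as the share. The sensitivity simulations used a log-rank test in place of the planned Weibull model.

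The correction should be made, because these figures are the trial's whole case for its sample size.

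**What to change.** 1. Rerun the existing simulation with an explicit share of participants who can have the event, over a range such as 10%, 17%, 25% and 40%. Include 12-month administrative censoring and the planned Weibull model.
2. State how low-risk participants are handled after their assessment, both in the simulation and in the primary analysis.
3. Replace the 95% and 83% statements in the abstract and the sample-size section with the resulting power and expected event counts for both sample sizes.
4. If a high power figure is kept, attach it to an outcome that nearly all participants can reach, such as time to first successful Fibroscan, and only after verifying it for that outcome.

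The cost is one rerun of existing code and some rewording. The correction itself needs no extra patients. The drawback is a stated power that is likely to be less favourable.

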#### Analysis of the primary outcome

We will use survival analysis methods to examine the primary outcome of time to diagnosis of high-risk NAFLD. We will use Kaplan–Meier plots to highlight any differences between the usual care and intervention groups. We will use parametric Weibull survival models to examine a statistical difference. We will check the parametric assumption and the model residuals.

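### The printed sample-size inputs (180 v 90 days, SD 10 days, 5% censored) do not reproduce the stated power of 83% at 156 and 95% at 234

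*Protocol article*

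**What the plan says.** All the inputs stand in the protocol article under Sample size and statistical power.

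- Effect: "We assumed an average diagnosis time of 180 days in the usual care group, and a halving of this time in the intervention group".
- Spread: "We assumed a log-normal hazard function with a standard deviation of 10 days".
- Censoring: "We assumed that 5% of participants would be censored due to death or loss to follow-up".
- Test level: "We used a two-sided 5% significance level".
- Results: "Two hundred and 34 participants will give us a 95% power to detect a 50% reduction", and "Our lower sample size of 156 gives us an 83% power".

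The powers came from 1,000 simulated data sets made with an R survival-simulation function. The code is cited by link. No hazard ratio, event share or other measure of spread is printed. Randomisation is 1:1, so the arms hold 78 or 117 participants. Under Primary clinical outcome, the event is a diagnosis of clinically significant fibrosis, with stiffness above 8.0 kPa. Follow-up is 1 year. The primary analysis section states: "We will use parametric Weibull survival models to examine a statistical difference".

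**The concern.** Once the effect is fixed as a halving of time, power depends on how widely diagnosis times vary and on how many participants have the event. The only spread printed is 10 days, against a difference between arms of 90 days. Waiting times that vary so little would make the two arms almost separate, and a trial of 156 or 234 would then have no reason to report 83% or 95% power. Something in the section is therefore misstated or left out.

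The minimum of 156, the target of 234 and the plan to approach 468 people all rest on this calculation. As printed, a reader cannot tell whether the trial has ample power or too little.

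**Working it through.** **Inputs.** Means 180 and 90 days, SD 10 days, 5% censored, two-sided alpha 0.05 (z = 1.960), 1:1 allocation, N = 156 or 234. The targets to reproduce are 83% and 95%.

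**1. SD of 10 days on the event times.** For a log-normal with mean m and SD s, the log-scale SD is √ln(1 + (s/m)²).

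- Usual care: √ln(1 + (10/180)²) = 0.0555, so 95% of times lie between about 161 and 200 days.
- LOCATE: √ln(1 + (10/90)²) = 0.111, so 95% lie between about 72 and 111 days.

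The ranges do not overlap, and the separation is 90/10 = 9 SDs. A log-rank simulation with 5% random censoring (2,000 runs) gave 91% power with 6 participants in total, 99.9% with 8, and 100% with 10, 156 and 234. A simulation fitting a Weibull model with 4 per arm (300 runs) rejected in every run.

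**2. Halving read as a hazard ratio of 2.** Schoenfeld's formula: power = Φ(½·√D·ln 2 − 1.960), with D the number of events.

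- N = 156: D = 0.95 × 156 = 148.2. ½ × √148.2 × 0.693 = 4.219, so power = Φ(2.259) = 98.8%.
- N = 234: D = 0.95 × 234 = 222.3. ½ × √222.3 × 0.693 = 5.167, so power = Φ(3.207) = 99.9%.

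**3. Other readings.**

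| Reading | N = 156 | N = 234 |
|---|---|---|
| Stated | 83% | 95% |
| Event times with SD 10 days | 100% | 100% |
| Hazard ratio 2, 95% events (Schoenfeld) | 98.8% | 99.9% |
| The same, Freedman's formula | 98.2% | 99.9% |
| Exponential times, 365-day censoring | 98.2% | 99.9% |
| Hazard ratio 2 on a log-normal baseline, SD 10 days | 97.3% | 99.8% |
| Hazard ratio 2 on a log-normal baseline, log-scale SD ln 10 | 98.6% | 100% |
| The same, with 365-day censoring | 95.4% | 99.0% |
| Log-normal times, halved, log-scale SD ln 10 (log-rank) | 39% | 54% |

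No row comes within 2 points of both stated powers.

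**4. What would give the stated powers.** The normal deviates for 83% and 95% power are 0.954 and 1.645.

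- *A wider spread.* Log-scale SD = ln 2 × √(0.95N) / (2 × (1.960 + z_power)). For N = 156: 0.693 × 12.17 / (2 × 2.914) = 1.45. For N = 234: 0.693 × 14.91 / (2 × 3.605) = 1.43. Simulation with a Weibull fit (500 runs) puts the match slightly lower, near 1.3 to 1.4.
- *Fewer events.* Events needed at a hazard ratio of 2: D = 4 × (1.960 + z_power)² / (ln 2)². For N = 156: 4 × 2.914² / 0.480 = 70.7, or 45.3% of participants. For N = 234: 4 × 3.605² / 0.480 = 108.2, or 46.2%. Taking 46% for both, Schoenfeld gives 83.5% and 94.9%.

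Each explanation fits both stated powers, so these are consistent with each other. Neither input is printed.

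**5. How much the missing inputs matter.** Weibull-fit simulations with 5% censored and events in everyone else gave, at N = 156 and 234: 96% and 99% for a log-scale SD of 1.0, 80% and 93% for 1.4, and 50% and 62% for 2.3. With a hazard ratio of 2, 5% loss and the event possible only in a given share of participants, Schoenfeld gives 76% and 90% for a share of 40%, and 64% and 81% for 30%. These spreads and shares are assumptions chosen to show the range, not figures from the article.

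**The case against.** The strongest reply is that step 1 takes one reading of an ambiguous sentence. The SD is attached to a hazard function, not plainly to observed times, and it may be a simulation setting described loosely. On a proportional-hazards reading with a baseline SD of 10 days, the gap is about 14 points at 156 (97.3% v 83%) and 5 points at 234 (99.8% v 95%). That is far less dramatic than a trial needing eight people. This stands, and it limits how much weight the eight-participant figure can bear. It does not remove the mismatch.

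A second reply is that the 5% covers only death and loss to follow-up and does not say that the other 95% have events. Only participants above 8.0 kPa can have the primary event, so the simulation may have used a much lower event share. This also stands as a possible explanation, but the section does not state such a share.

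A third reply is that the code is cited. The code could settle the cause, but a link does not make the printed inputs agree with the printed powers.

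A reader might also object that the simulation uses a log-normal hazard while the analysis is Weibull. The article does not support treating that as an error. Generating data from one distribution and analysing them with another is legitimate, the section does not say which model was fitted to the simulated data, and the analysis section plans a check of the parametric assumption.

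**Conclusion.** The mismatch is established. The inputs as printed give about 100% power on the literal reading, or 98.8% and 99.9% at a hazard ratio of 2 with 95% events, against 83% and 95% stated. The log-rank and normal-approximation checks stand in for the planned Weibull model. That is immaterial at a 9-SD separation, where the Weibull fit gave the same answer.

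The cause is not established. It may be the SD's value, its unit or scale, the stated powers, or an unstated event share. Three stronger conclusions might be inferred, and the article supports none of them:

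- *A log-scale SD near 1.4 must be the true input.* An event share of about 46% at a hazard ratio of 2 fits equally well.
- *The trial is far larger than it needs to be.* That takes the 10 days as a real spread of waiting times, and the stated powers themselves speak against it.
- *The trial is underpowered.* That depends on a spread and an event share that the article does not give.

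Confidence is high for the mismatch only. The stated power should not be relied on until the section is reconciled.

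**What to change.** Reconcile the sample-size section with the simulation code, then:

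1. Correct the SD statement, giving the value, the scale (days or log-days, event times or hazard) and its source. The two clinics' existing waiting-list records would be a suitable source.
2. State the share of participants assumed to have the primary event within follow-up, separately from the 5% lost or dead.
3. Say whether the halving was simulated as a ratio of times or as a hazard ratio.
4. Rerun the simulation with the planned Weibull analysis and restate power at 156 and 234 over a plausible range of spreads and event shares.

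The cost is a rerun of existing code and a few corrected sentences. The drawback is that the restated power may be less favourable, which could reopen the choice of 156 as the minimum or 234 as the target.
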